### Patient and public involvement statement

In addition to the previously mentioned theoretical framework mentioned, we conducted focus groups with patients who have diabetes and depression to select key and effective outcomes and instruments for our study. The insights gained from these efforts were reviewed by study team, who then transformed these identified needs into research questions to be studied.

The concept of patient and public involvement also guided CIC-PDD model development. Since the core of IC is patient-centered care, before designing research plan and finalizing CIC-PDD model, we conduct multiple interviews with key stakeholders (especially patients) and engaged in multiple rounds of analysis, demonstration, and revision.

### Supervision and fidelity

CMs will receive ongoing supervision from health communicator and study staff. CMs need to keep and maintain notes for the patients using the “Follow-up Manual” during every session. This “Follow-up Booklet” reports how many sessions patients received, the delivery mode (in person or by telephone) in which they received intervention, PHQ-9 scores, blood glucose level, and what interventions patients accepted.

For each session, CMs are required to make audio recordings and take photos to document the process and capture important information. At the end of session, the CMs need to send the recorded materials to health communicator, who will review and evaluate them. A random selection of these materials will then be submitted to the study team for further assessment and analysis.

Second, the health communicator will also confirm whether the CMs conduct follow-up according to care plan from the patient’s perspective through regular e-visits.

Third, we will hold regular meetings with the directors of the CHCs, public health officials, and local health officials to ensure the fidelity of the CIC-PDD from the organizational perspective.

### Study setting

The study sites are 8 CHCs from two counties of Weifang, Shandong, a province in eastern China. There are several reasons for choosing Weifang as our study settings. First, this is a priority city for several initiatives to strengthen primary care, including the integrated chronic diseases care approach and the establishment of single disease group management. Additionally, Weifang is a national pilot city for the construction of social psychosocial service system designated by China National Department of Health, making it feasible to conduct the interventions of both mental and physical conditions. Furthermore, both selected counties have tertiary hospitals, which can meet the need for a multidisciplinary team of specialists.

Recruitment of CHCs ran from July 2021 to November 2021.

### Randomization and recruitment

#### Randomization

We randomized CHCs in each county on a 1:1 ratio, with an equal number of CHCs (*n* = 4) in each group. The allocation to the two arms was balanced based on size of the cluster, using the number of diabetic patients in each cluster.

Before implementation, allocation of clusters to each study arm was conducted by a statistician at the Peking University China Center for Health Development Studies. The statistician was not involved in implementation of the study.

To reduce the likelihood of bias caused by contamination and type II errors, cluster randomization was chosen. Patients within the clusters are allocated to the same group as their PCPs.

See Fig. 1 for an illustration of the randomization process.

#### Sample size and power calculations

The study is powered to detect between-arm differences in achieving the primary outcome at 12 months post-randomization. Based on previous literature [47], a sample size of 480 patients (240 per group) at 8 CHCs offered greater than 80% power (*α* = 0.05; intraclass correlation coefficient 0.03) to detect a 20% absolute risk difference between groups on the primary outcome. To account for a potential 10–15% loss to follow-up (e.g., leave the area, die or refuse to take part in the study at follow-up) and to provide greater robustness against type II error, 280 cases were included in each of the two groups in the actual study. According to our previous systematic review [28], previous study sample sizes ranged from 58 to 417. Therefore, we expect that our study will have the largest sample size and, consequently, the highest efficiency and statistical power.

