***Effectiveness***				
Individual	Primary outcomes	▪ Primary outcomes: glycemic control (HbA1c); depression symptoms scores (SCL-20)	Health records; survey data	Quantitative
	Mental and physical health outcomes:	▪ Proportion of participants achieving significant reductions in individual outcomes: [50% ≥ reduction in SCL-20], [HbA1c ≥ 0.5% reduction]	Survey data	Quantitative
	Change in quality of life	▪ SF-12 ▪Diabetes Quality of Life	Survey data	Quantitative
	Experience of holistic patient-centered care	▪PACIC ▪Satisfaction with care	Interview data (interviews with patients); survey data	Qualitative & quantitative
	Person-centered care	▪PCCA	Survey data	Quantitative

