##### Primary outcome

The primary outcome in this trial is the change in depression symptoms scores (The Symptom Checklist-20, SCL-20) and glycemic control (HbA1c) from baseline to 6 and 12 months.

The use of the SCL-20 for outcome measurements is intended to minimize potential test–retest bias given the repeated use of the PHQ-9 for clinical care.

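### The stated power is for a 20-point difference in proportions, but both primary outcomes are changes in continuous measures, so it applies to neither primary comparison

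*Protocol article*

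**What the plan says.** The protocol article, under Sample size and power calculations, opens with: "The study is powered to detect between-arm differences in achieving the primary outcome at 12 months post-randomization". It then says that "a sample size of 480 patients (240 per group) at 8 CHCs offered greater than 80% power", with alpha and clustering given as "0.05; intraclass correlation coefficient 0.03", "to detect a 20% absolute risk difference between groups on the primary outcome". To allow for 10–15% loss, 280 per group were enrolled. No control-arm rate, mean difference or SD is given.

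Under Primary outcome the article says: "The primary outcome in this trial is the change in depression symptoms scores (The Symptom Checklist-20, SCL-20) and glycemic control (HbA1c"), measured "from baseline to 6 and 12 months". Table 1, in its Effectiveness block, agrees: "Primary outcomes: glycemic control (HbA1c); depression symptoms scores (SCL-20").

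The binary versions appear under Secondary outcomes, and in a separate row of Table 1, as "Proportion of participants achieving significant reductions in individual outcomes". They are a reduction of at least 50% in SCL-20 and a reduction of at least 0.5% in HbA1c.

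**The concern.** A 20% absolute risk difference can be the effect size only for an outcome that each patient either achieves or does not. Neither primary variable is of that kind. The sample-size paragraph reads as if there were a single responder-type primary outcome, and the outcome sections define two continuous ones. The article does not leave the basis for power to another document. It states one that does not fit the outcome it defines.

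Two things are at stake. Readers will take the figure of more than 80% as the sensitivity of the SCL-20 and HbA1c comparisons, for which the article states no power. And while the two sections disagree, it is unclear whether mean change or response is the primary analysis, which leaves room to choose after the results are known.

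**Working it through.** **Inputs from the article:** 240 per arm; 8 centres, 4 per arm; ICC 0.03; alpha 0.05; 20-point risk difference.

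**Assumptions made here:** two-sided test, equal cluster sizes, the same ICC for both measures, no baseline adjustment. The 6 df reference (8 clusters minus 2) is a small-sample choice that the article does not state.

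**Effective sample size**
- Patients per centre: 240 / 4 = 60.
- Design effect: 1 + (60 − 1) × 0.03 = 2.77.
- Effective n per arm: 240 / 2.77 = 86.6.

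**The article's own figure.** Without a control rate it cannot be reproduced exactly, so the rate was varied. Worked example, 20% v 40%:
- Null SE: √(2 × 0.30 × 0.70 / 86.6) = 0.0696.
- Alternative SE: √((0.20 × 0.80 + 0.40 × 0.60) / 86.6) = 0.0679.
- Power: Φ((0.20 − 1.96 × 0.0696) / 0.0679) = Φ(0.94) = 82.5%.

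| Control v intervention | Power (normal) |
|---|---|
| 10% v 30% | 91.5% |
| 20% v 40% | 82.5% |
| 25% v 45% | 79.3% |
| 30% v 50% | 77.1% |
| 40% v 60% | 75.4% |
| 60% v 80% | 82.5% |

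The claim is attainable for some control rates and not for others. On 6 df, 20% v 40% gives 69%. The allowance for loss is consistent: 240 / 0.90 = 267 and 240 / 0.85 = 283, against 280 enrolled. None of this is power for a mean change.

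**Continuous scale, in SD units** (no SD is given)
- SE of a standardised difference: √(2 / 86.6) = 0.152.
- Two-sided alpha 0.05, 80% power, normal: (1.96 + 0.84) × 0.152 = 0.43 SD.
- The same on t with 6 df: required noncentrality 3.37, so 3.37 × 0.152 = 0.51 SD.
- Two-sided alpha 0.025, normal: (2.24 + 0.84) × 0.152 = 0.47 SD.
- The same on 6 df: 3.94 × 0.152 = 0.60 SD.

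With 15% loss from 280 (238 analysed per arm), the alpha 0.05 values are still 0.43 and 0.51 SD.

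**Which alpha applies depends on the success rule.** If both outcomes must succeed, each is tested at 0.05 and the 80% is per outcome. Joint power is lower: 0.80 × 0.80 = 64% if the two were independent. If either may succeed, 0.025 each is the simple split.

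**Is the 20-point effect harder to detect on the continuous scale?** Suppose response means that a normally distributed change crosses a cut-off. The implied shift is z(p + 0.20) − z(p): 0.51 SD for 40% v 60%, 0.59 SD for 20% v 40%, and 0.76 SD for 10% v 30%. At SE 0.152 and alpha 0.05, power over this range is about 92% to 99% (normal) or 79% to 98% (6 df).

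**The case against.** The strongest reply is that the mismatch does no harm. Under the normal-shift assumption, an effect as large as the one planned for would be detected about as well, or better, on the continuous scale. Enrolment is complete, so rewording changes neither the number of patients nor the estimate. The final confidence intervals will show the precision achieved, and the full protocol, available on request, may hold the responder definition and control rate.

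Much of this stands. A reader might infer that the sample is too small, or that the trial's real sensitivity is worse than claimed. The documents do not support either inference: with no target mean difference or SD, adequacy cannot be judged. The planned adjustment for baseline characteristics would be expected to lower the detectable difference as well.

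A reader might also take 0.5 HbA1c points as the target difference between arms and calculate a low power from it. In the article, 0.5% is a threshold for the individual patient's reduction. It is not a difference between arm means, and no SD is given, so any such percentage is at most illustrative.

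What the reply does not remove is the contradiction. The article attaches its power figure to the primary outcome, and no primary outcome it defines can have a risk difference. If the responder measure was the intended primary, the outcome sections are wrong instead.

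**Conclusion.** The point holds as a contradiction between the sample-size section and the outcome definitions. The figure of more than 80% power for a 20-point risk difference does not apply to change in SCL-20 or to change in HbA1c, and one statement is made to serve two primary variables with no rule for combining them. The detectable differences are 0.43 to 0.51 SD per outcome at alpha 0.05, or 0.47 to 0.60 SD at 0.025 each. The lower figure of each pair uses the normal reference and the upper uses 6 df. They rest on the assumptions listed above, chiefly a common ICC of 0.03 and no baseline adjustment. They describe what the design can detect and do not show that it is underpowered.

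**What to change.** Reconcile the Sample size and power calculations section with Primary outcome, Secondary outcomes and Table 1:

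- Attach the 20% risk difference to the secondary responder outcome, name which of the two responder measures it refers to, and give the assumed control rate.
- For change in SCL-20 and change in HbA1c at 12 months, state the detectable difference with its assumptions labelled (240 analysed per arm, 8 centres, ICC 0.03 for both, no baseline adjustment, reference distribution). Use 0.43 SD (normal) or 0.51 SD (6 df) at two-sided 0.05 if both must succeed, noting that joint power is lower. Use 0.47 or 0.60 SD at 0.025 each if either may succeed.
- State which success rule applies.
- Name the responder outcome as primary only if the approved protocol versions (1.1 or 1.2) show that it was prespecified as such. Recruitment has closed, so a change without that evidence would be a switch of primary outcome.
- Give no HbA1c power percentage based on the 0.5% threshold unless it is labelled illustrative and its SD is stated.

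The cost is a reworded sample-size section. No extra patients are needed.

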#### Blinding

First, participants are not blinded to their treatment arms (as it is impossible to conceal the fact of collaboration or lack of it from the patients).

Second, it is not possible to blind care team since they are required to participate in additional training activities, as well as the introduction of specialist team and health communicator.

Third, all recruited outcome assessors are blinded to the status of the patient group and work independently of the intervention team and study team.

Finally, the groups are coded and anonymized to ensure that researchers are blinded throughout the entire analysis and writing process.

The design is open label with only outcome assessors being blinded so unblinding will not occur.

#### Patient screening and recruitment

Recruiting patients is often considered the most challenging part of conducting a cluster randomized controlled trial (RCT) [48]. Failing to recruit the desired number of participants can lead to costly and time-consuming extensions, as well as a decrease in statistical power.

To overcome these problems, we employ a two-phase approach to patient recruitment: initial screening and eligibility testing. The target population for this study consists of diabetic patients who are over 18 years old and exhibit depressive symptoms (indicated by a PHQ-9 score ≥ 10). Based on the estimated prevalence of depression among individuals with diabetes, we anticipate screening 4000 diabetes patients to achieve the desired sample size.

##### Initial screening

PCPs will contact diabetic patients and provide them with brief information about the CIC-PDD project, without mentioning terms related to depression. Then, PCPs will review existing electronic health records to identify preliminary qualified participants with diabetes. PCPs will receive compensation for initial screening.

##### Eligibility testing

Individuals who are found eligible after the initial screening will have the study details fully explained to them, and they will be invited to complete an eligibility test assessment through telephone or face-to-face surveys. During this phase, PCPs will conduct a detailed eligibility test questionnaire with potential participants.

To be eligible for the study, participants must meet the following inclusion criteria:Age ≥ 18 and ≤ 85 years, and;Confirmed diagnosis of diabetes, and;PHQ-9 score ≥ 10, and;Not serious hearing or vision impairment, able to complete telephone interviews, and;Willingness to consent to randomization.

The PHQ-9 can be administered either in person or by telephone with similar results, making telephone assessments an effective method for screening for depression in PHC [49].

If any of the following conditions exist, individuals will be excluded from participation:Have a serious medical condition and/or are in an advanced stage (e.g., heart disease, kidney failure, cancer, major organ failure), or;Have been diagnosed with bipolar disorder or schizophrenia, are currently on antipsychotic medication or mood stabilizers, or require psychiatric treatment in a medical facility, or;Have active suicidal thoughts and intent (item # 9 of the PHQ-9), or;Are pregnant or lactating, or;Live in a long-term care facility, or;Currently participate in other clinical trials, or;No fixed address or contact details, or;PCPs have removed them from the practice diabetes database, or;For other reasons, the PCPs considered it unsuitable to participate in this study.

The flow diagram of the recruitment and screening strategy is shown in Fig. 1.

#### Informed consent procedure

##### Consent to be screened for eligibility

During the initial screening, PCPs will provide patients with verbal informed consent for brief notification of the project and the need to review their health records. During the eligibility testing phase, the PCPs will obtain informed consent from patient in-person or by telephone. They will introduce the details of the CIC-PDD project, including the content of the intervention, group assignment, and follow-up assessment, while also conducting the recruitment process simultaneously.

##### Consent to participate in the trial

Within 1 month of the eligibility testing appointment, the study staff will contact PCPs and send the name list of patients who meet the inclusion criteria. Participants will be recruited into the study following contact of the PCPs and will be set up baseline assessments (offline) that will be conducted by blinded outcome assessors. Participants will provide written consent before completing the baseline questionnaire.

In the informed consent document, participants will be explicitly queried regarding their willingness to permit the utilization of their data in the event of their withdrawal from the trial. Additionally, participants will be asked to grant permission to the research team for sharing pertinent data with individuals from Peking University engaged in the research or relevant regulatory authorities, as appropriate. Importantly, this trial does not encompass the collection of biological specimens for storage.

### Data collection plan

Following the completion of the trial, all collected data will undergo analysis to develop an implementation blueprint. The outcomes, measures, and methods presented in this protocol have been evaluated for relevance and feasibility, and they were designed in collaboration with key stakeholders.

The data for the CIC-PDD project consists of interviewer-based data (face-to-face) and register data. Participants are interviewed face to face at baseline, and again after 6 and 12 months. Data collection through interviews will be conducted by outcome assessors trained in the specific instruments.

See Table 1 for schedule of enrolment, interventions, and assessments.

**Table 1 Tab1:** Schedule of enrolment, interventions and assessments

Assessment level	Construct	Metric/Measure	Data Sources	Data type
***Reach***				
Individual	Characteristics of patients	▪ Eligibility criteria	Health records; Survey data	Quantitative
		▪ Demographic information	Survey data	Quantitative
		▪ Characteristics of patients who screened positive depression	Survey data	Quantitative
		▪ Characteristics of patients who were lost to follow-up	Document review (CIC-PDD project records)	Qualitative
Organization	Characteristics of CMs	▪ Characteristics of CMs who implement follow-ups according to the care plan		
	Contextual factors	▪ Ability to identify and manage targeted patient populations	Interview data (Study team and CMs)	Qualitative
		▪ Identified facilitators and barriers to recruitment	Interview data (CFIR interviews with CMs)	Qualitative
		▪ Identified recommendations for improvement	Interview data (CFIR interviews with care team)	Qualitative
***Effectiveness***				
Individual	Primary outcomes	▪ Primary outcomes: glycemic control (HbA1c); depression symptoms scores (SCL-20)	Health records; survey data	Quantitative
	Mental and physical health outcomes:	▪ Proportion of participants achieving significant reductions in individual outcomes: [50% ≥ reduction in SCL-20], [HbA1c ≥ 0.5% reduction]	Survey data	Quantitative
	Change in quality of life	▪ SF-12 ▪Diabetes Quality of Life	Survey data	Quantitative
	Experience of holistic patient-centered care	▪PACIC ▪Satisfaction with care	Interview data (interviews with patients); survey data	Qualitative & quantitative
	Person-centered care	▪PCCA	Survey data	Quantitative
***Adoption***				
Individual	Characteristics of care team	▪ Characteristics of CMs, health communicators and specialists participating in CIC-PDD project	Document review (CIC-PDD project records)	Qualitative & quantitative
Organization	Characteristics of CHCs	▪ Criteria for CHCs participation	Document review (CIC-PDD project records)	Qualitative & quantitative
		▪Features of participating CHCs	Document review (CHCs documents)	Qualitative & quantitative
		▪ Comparison of characteristics between intervention CHCs and control CHCs	Survey data	Quantitative
		▪ Description of usual care in control CHCs	Document review (CHCs documents)	Qualitative
		▪ CHCs’ Readiness: ORIC	Survey data	Quantitative
	Contextual factors	▪ Perception of extent to which CIC-PDD project has been adopted by CHCs and modified to fit their context	Interview data (CFIR interviews with CMs, the directors of the CHCs, public health officials)	Qualitative
		▪ Identified facilitators, barriers, and recommendations at organizational level	Interview data (CFIR interviews with care team)	Qualitative
***Implementation***				
Individual	Patients’ compliance	▪ The use of “Health Education Manual” and “Health Diary”	e-visits	Qualitative & quantitative
	Change in behaviors and perceptions:	▪ Self-management: SDSCA Burden of illness: MTBQ Burden of treatment: MMAS	Survey data	Quantitative
Organization	Development of CICPDD	▪ Development of materials (e.g., Work Manuals); data collection protocols and forms	Document review (CIC-PDD project records)	Qualitative
	Processes	▪ Screening, recruitment and outcomes assessments	Document review (CIC-PDD project records)	Qualitative
	Training	▪ Detailing training sessions, and training contents and materials provided; formal and written post-training tests; feedback of training	Document review (CIC-PDD project records); survey data	Qualitative & quantitative
	Service delivery	▪ Follow-up sessions, specialist consultations; time and frequency of service delivery; case review	Document review (CIC-PDD project records)	Qualitative
	Care team attitudes and perceptions	▪ Baseline clinician attitudes survey ▪ LIM ▪ Project Satisfaction ▪ Perceptions of Working in a Primary Health Care Team	Survey data	Quantitative
	Fidelity	▪ Completion of “Follow-up Booklet”	Document review (CIC-PDD project records)	Qualitative
		▪ CIC-PDD Adherence Questionnaire	Survey data	Quantitative
		▪ Extent to which project is delivered and received as intended	Interview data (CFIR interviews with care team and patients); document review (CIC-PDD project records)	Qualitative
	Contextual factors	▪ Identified facilitators and barriers to implementation	Interview data (CFIR interviews with CMs)	Qualitative
		▪ Identified recommendations for improvement	Interview data (CFIR interviews with health communicators)	Qualitative
	Economic Evaluation	▪ Reduction in costs; the relative cost-effectiveness	Survey data; health records	Quantitative
***Maintenance***				
Individual	Patients’ gains	▪ Knowledge and skills acquired	NPT interviews with patients; survey data	Qualitative & quantitative
		▪ Stability of effects of the CIC-PDD project on patient-level outcomes of effectiveness over time	Interviews with intervention group participants	Qualitative
Organization	PCPs’ gains	▪ Knowledge and skills acquired	NPT interviews with CMs	Qualitative
	Transform into practice	▪ Integration of aspects of the model into routine practice	NPT interviews with CMs	Qualitative

*CMs*, case managers; *CHCs*, community health centers; *CFIR*, Consolidated Framework for Implementation Research; *SCL-20*, The Symptom Checklist-20; *SF-12*, The12-Item Short Form Health Survey; *PACIC*, Patient Assessment of Chronic Illness Care; *PCCA*, Patient-Centered Care Assessment Tool; *ORIC*, Organizational Readiness for Implementing Change; *SDSCA*, Summary of Diabetes Self-Care Activities Questionnaire; *MTBQ*, Multimorbidity Treatment Burden Questionnaire; *MMAS*, Morisky Medication Adherence Scale; *LIM*, Level of Integration Measure; *NPT*, Normalization Process Theory

